## Abstract

**Background:** Prostate cancer is the most common non-cutaneous malignancy in men. Today most patients may expect to live years following the diagnosis and may thus experience significant morbidity due to disease progression and treatment toxicity. In order to address some of these problems exercise has been suggested and previously studies have shown improvements of disease specific quality of life and a reduction in treatment-related toxicity. Cohort studies with long term follow up have suggested that physical activity is associated with improved survival in prostate cancer patients. Previously one randomised controlled trial has examined the efficacy of football in prostate cancer patients undergoing androgen deprivation therapy to usual care and reported positive effects on lean body mass and bone markers. Against this background, we wish to examine the effectiveness of community-based football for men diagnosed with prostate cancer.

**Methods:** Using a randomised controlled parallel group, multicenter, superiority trial design, two hundred prostate cancer patients will be recruited and randomised (1:1) to either community-based football one hour twice weekly or to a control group. The intervention period will be six months. The primary outcome is quality of life assessed after 12 weeks based on the change from baseline in the Functional Assessment of Cancer Therapy–Prostate questionnaire. Secondary outcomes are change from baseline to six months in quality of life, lean body mass, fat mass, whole body and regional bone markers, as well as physical activity and functional capacity at 12 weeks and six months. Safety outcome variables will be falls resulting in seeking medical assessment and fractures during the six-month period.

**Discussion:** Football is viewed as a case for non-professional, supervised community-based team sport for promoting long-term physical activity in men diagnosed with prostate cancer. This randomised trial will provide data on effectiveness and safety for men with prostate cancer when football training is delivered in local football clubs.

**Trial registration:** Clinicaltrials.gov identifier: NCT02430792

**Keywords:** Prostate cancer, Soccer, Exercise, Physical activity, Quality of life

\* Correspondence: [contact]

University Hospitals Centre for Health Research (UCSF), Rigshospitalet, University of Copenhagen, Copenhagen, Denmark

Full list of author information is available at the end of the article

[figure not shown]

## Background

Prostate cancer (PCa) is the most frequently diagnosed non-cutaneous cancer in men worldwide [1]. In comparison to most other malignant diseases, PCa progresses slowly. Presently more than 90 % of all cases of PCa are detected early, with the 10 and 15-year relative survival rates at 98.8 and 94.3 %, respectively [1]. However, treatment of PCa is often associated with side effects and as the patients are likely to survive many years following diagnosis and primary treatment, quality of life (QoL) is of growing interest. PCa patients managed with hormonal therapy face an elevated risk of becoming overweight and for developing metabolic syndrome, type 2 diabetes and cardiovascular disease [2], which regular physical activity may counteract. Despite this fewer than half of men living with PCa follow the official physical activity guidelines [3]. Moreover, unlike many other cancer patient groups, PCa patients do not change their health behaviour spontaneously after being diagnosed [4]. Cohort studies examining the relationship between physical activity and disease progression and survival in men with PCa have shown that vigorous activity is associated with better outcomes [5–7].

Recent systematic reviews of exercise intervention trials in men with PCa indicate that exercise has a beneficial effect on muscular fitness, cardio-respiratory fitness, functional task performance, lean body mass (LBM), fatigue and QoL [8–10]. Furthermore exercise has been shown to meet the requests male cancer patients have for active, rational activities [11, 12]. The vast majority of existing trials, however, have examined the effects of hospital-based, short-term and cost-intensive exercise interventions with a short follow-up period and low degree of adherence [13]. Therefore the long-term effects and applicability of interventions promoting physical activity remain undocumented [14].

Participation in sport is acknowledged as important for public health [15]. The most common sport for men in Denmark and many other countries is football [16]. Growing evidence suggests that recreational football, i.e. non-tournament-based small-sided games, can have significant health promoting effects in various populations [17–19]. It has also been shown that football may provide peer-to-peer psychosocial support and improve social capital [20], potentially increasing long-term adherence. Therefore, we recently examined the efficacy of recreational football in men with PCa undergoing androgen deprivation therapy (ADT). The results show that the football training improved LBM, muscle strength and markers of bone strength [21, 22] and that men experience football as an opportunity to regain control and responsibility for their own health without being in the role of patient [23].

Usual care for men with PCa in Denmark is rehabilitation (often aerobic and/or strength training) offered by local authorities. However, substantially fewer men than women (30 vs. 70 %) participate in rehabilitation [24], indicating that rehabilitation efforts might should be gender-oriented [25]. In this study, the participants in the control group are informed of the official physical activity guidelines and advised to continue their daily living, as they normally would do, not guiding them to other interventions neither preventing them to do so.

Thus, we will examine if recreational football, delivered in local football clubs (i.e. community-based), may complement existing rehabilitation approaches by promoting adherence to exercise and improving QoL and physiological health measures.

## Objective

The primary objective of the FC Prostate Community Trial (FCPC) trial is to determine whether community-based football is superior to usual care for improving cancer-specific QoL after 12 weeks of participation.

The secondary objectives are to determine whether community-based football is superior to usual care for improving PCa-specific QoL, lean body mass, fat mass, bone mineral density and bone mineral content after six months and functional well-being and physical activity after 12 weeks and after six months. The safety of the intervention will also be evaluated based on falls resulting in seeking medical assessment and fractures after six months.

## Methods

### Trial design

The FCPC Trial is a randomised controlled parallel-group superiority trial with two parallel groups (community-based recreational football and usual care) that examines QoL after 12 weeks as the primary endpoint. Participants will be randomised (1:1) and the trial design is pragmatic [26].

### Participants

Patients age 18 years or older diagnosed with PCa, able to read and write Danish and willing to sign an informed consent are eligible for participation in the study. Patients cannot be included if they have undergone prostatectomy within six weeks prior to participation, are prohibited from participating in football training by their primary physician or have a hip or spine BMD T-score lower than  $-2.5$  (i.e. the criterion for osteoporosis). Table 1 lists the eligibility criteria.

Patients will be recruited from urological clinics, which will provide information on the study and promote

**Table 1** Eligibility criteria

| Inclusion                                                                                                                                                                                                                       | Exclusion                                                                                                                                                                                             |
|---------------------------------------------------------------------------------------------------------------------------------------------------------------------------------------------------------------------------------|-------------------------------------------------------------------------------------------------------------------------------------------------------------------------------------------------------|
| 
 
Patients diagnosed with prostate cancer
 
Age: <math>\geq 18</math> years
 
Able to read and complete questionnaires in Danish
 
Signed informed consent
 
 | 
 
< 6 weeks prostatectomy
 
Football training not allowed by primary physician
 
Hip or spine bone mineral density < -2.5 T-score
 
 |

patients to participate in the study. Figure 1 presents a timeline for participation and the trial design.

Study sites and recruitment status are available at clinicaltrials.gov under trial registration number NCT02430792.

### The football intervention

Participants allocated to the intervention group will be offered one hour of recreational football twice weekly. The football training sessions consist of a 20-min warm-up based on the FIFA11+ concept, though modified to suit older players [27]. Next, participants will spend 20 min practising dribbling, passing and shooting. The training sessions will then end with 20 min of 5–7-a-side football. Two coaches recruited from the local football club will be in charge of all training sessions. The coaches are expected to have experience as either a player or coach but no other formal qualifications are required. The coaches will be required to have passed a first-aid course and to complete a 10-h course involving lectures on PCa treatment, patient experiences of PCa and a manual describing the content of the training, including the FIFA 11+ concept intended to prevent injuries. Participants will be told to avoid hard tackles and other actions that carry a risk of injury. In the event of injuries participants will remain in their allocated group and will be encouraged to participate in football practice again after recovery. Adherence to the intervention will be recorded by the coaches. Participants

allocated to football training will be able to track their individual adherence and compare it to an average adherence rate of participants in the football group. A logical model, presented in Table 2, summarises the key inputs, activities and intended outputs of the intervention, while Fig. 2 presents the activities and Fig. 3 shows the assumed causal pathways for the effect of the intervention on the individual.

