### Sample size and power considerations

The sample size calculation is based on the detection of a minimal clinical important difference between groups on six points on the FACT-P questionnaire [28] at 12 weeks with a standard deviation of 15 FACT\_P points. A two-sided significance level of 5 % and power of 80 % were chosen; The standard deviation is based on a previous exercise trial [30] but increased slightly as FCPC participants will be more heterogeneous than the participants in that trial. Consequently, 100 participants will be needed in each group, i.e. 200 participants in total, in order to detect a statistically significant difference between groups. No interim analysis will be performed. However, if the

anticipated sample size has not been enrolled by 1 May 2017, recruitment will end and final analyses will be performed with the number of patients recruited at that point.

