### Primary outcome

The continuous FACT-P outcome score will be calculated using the official scoring guideline. As described in the scoring guideline missing items will be prorated by multiplying the sum of the subscale with the number of the items in the subscale, then divided by the number of items answered. This will be done if more than 50 % of the items are answered in the subscales and 80 % are answered in the total questionnaire. The change score of the total FACT-P at 12 weeks will be calculated by subtracting the total 12-week score from the respective trial participant's baseline score. Analysis of covariance will be used [32], group and ADT status will be set as factors, the response will be change in FACT-P and covariates will be age and baseline score. The results will be presented as least squares means (LSMEANS) differences between the two groups with 95 % confidence intervals and *p*-values.

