### Secondary outcomes including safety outcomes

Changes from baseline to six months for LBM, BMD, BMC and total body fat mass will be analysed in the same manner as the primary outcome.

QoL, functional well-being and physical activity (based on metabolic equivalent of task values derived from IPAQ) measured at baseline, 12 weeks and six months will be analysed using a mixed model for repeated

measurements. Changes from baseline to 12 weeks or six months will be treated as the response. The model will include fixed effects of factors: group, ADT, sampling time and their interactions, and the analysis will be adjusted for age and baseline value. The correlation between measurements on the same participant will be modelled using a random effect of participant.

Safety outcomes will be listed for each group and the number of falls that resulted in seeking medical assessment and fractures will be compared across groups using Fisher's exact test.

Subgroup analyses will be reported for the patients treated with ADT, which means that results will be given for both the overall treatment effect and for the subgroup obtained by stratifying according to ADT. To verify the credibility of our subgroup analyses, we will apply the criteria proposed by Sun and colleagues [33], i.e. the subgroup variable is a baseline characteristic, a stratification factor, specified a priori and includes only a small number of analyses.

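### The planned models and sample size have no term for football club, so the 5 % type I error is not held if outcomes vary between clubs in the football arm

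*Protocol*

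**What the plan says.** Under The football intervention, men in the intervention arm train together twice weekly and each session ends in a small-sided game of 5 to 7 a side. On staffing: "Two coaches recruited from the local football club will be in charge of all training sessions". Under Control group, the comparison arm gets a short phone call and an email, with no grouping. Randomisation is of individuals, stratified by centre and androgen deprivation (ADT) status.

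The Background gives a reason why team-mates' outcomes might move together: "football may provide peer-to-peer psychosocial support and improve social capital".

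The analysis sections fix the models. For the primary outcome: "Analysis of covariance will be used [32], group and ADT status will be set as factors", with age and baseline score as covariates. The DXA outcomes follow the same model. For the repeated measures: "The correlation between measurements on the same participant will be modelled using a random effect of participant". Neither model has a term for club, coach or centre.

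The sample size section uses a "minimal clinical important difference between groups on six points on the FACT-P questionnaire" "with a standard deviation of 15". It continues: "A two-sided significance level of 5 % and power of 80 % were chosen", and concludes that "100 participants will be needed in each group, i.e. 200 participants in total". No ICC, cluster size or design effect enters.

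**The concern.** Grouping exists in one arm only, so this is an individually randomised trial that is partially nested. Men at one club share coaches, team-mates and setting. Coaches need playing or coaching experience, a first-aid course and a 10-hour course but no other formal qualification, so delivery may differ between clubs. FACT-P has a social/family domain, so the primary outcome partly measures something that a team could share.

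If such differences exist, the mean of the football arm carries between-club variance that the ANCOVA does not count. The confidence interval is then too narrow, and the 5 % limit on type I error set in the statistical methods is exceeded. This matters for the stated purpose, because the Discussion wants results that generalise and that inform decisions on using community clubs.

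The protocol names the model, its factors, covariates and random effect. It has therefore fixed a specification without a club term, and has not merely left detail to a later document.

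**Working it through.** **Inputs from the protocol:** difference 6, SD 15, two-sided 5 %, power 80 %, 100 per arm.

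**Assumed, because the protocol gives none:** men per club m, and club ICC. The only hint of size is the 5 to 7-a-side game, which implies 10 to 14 men if one game is played. I use m = 10, 14 and 20, which for 100 men means about 10, 7 and 5 clubs, and ICC 0.01 to 0.05.

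**Step 1, the protocol's figure.** n per arm = 2 × (15 × (1.960 + 0.842) / 6)² = 98.1, so 99. The t-based version gives 99.1, so 100. The stated 100 reproduces, and it is the figure for independent observations. Power at 100 per arm is 80.7 % (normal) or 80.4 % (t).

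**Step 2, clustering in the football arm only.**
- Design effect DE = 1 + (m − 1) × ICC, applied to the football arm.
- Standard error assumed by the plan = 15 × √(2/100) = 2.12.
- True standard error = 15 × √((1 + DE)/100).
- Type I error of the planned test = 2 × (1 − Φ(1.96 × 2.12 / true SE)).
- Power of a test adjusted for a known ICC = Φ(6 / true SE − 1.96).

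Example, m = 14 and ICC 0.05: DE = 1.65; true SE = 15 × √(2.65/100) = 2.44; ratio 1.151; type I error 8.9 %.

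| m | ICC | True SE / planned SE | Type I error, planned test | Power, adjusted test | n per arm for 80 % |
|---|---|---|---|---|---|
| 10 | 0.01 | 1.022 | 5.5 % | 79.0 % | 103 |
| 10 | 0.02 | 1.044 | 6.0 % | 77.3 % | 107 |
| 10 | 0.05 | 1.107 | 7.7 % | 72.4 % | 121 |
| 14 | 0.01 | 1.032 | 5.8 % | 78.3 % | 105 |
| 14 | 0.02 | 1.063 | 6.5 % | 75.8 % | 111 |
| 14 | 0.05 | 1.151 | 8.9 % | 69.0 % | 130 |
| 20 | 0.01 | 1.046 | 6.1 % | 77.1 % | 108 |
| 20 | 0.02 | 1.091 | 7.2 % | 73.7 % | 117 |
| 20 | 0.05 | 1.214 | 10.7 % | 64.4 % | 145 |

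Simulation of the unadjusted two-group test (20,000 trials per setting) agrees: 6.0 % and 7.6 % for 10 clubs of 10 at ICC 0.02 and 0.05, and 7.3 % and 10.7 % for 5 clubs of 20.

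**Step 3, part of the clustering shared with controls.** Assume one club per centre and K centres, and let a share s of the football-arm ICC be a centre effect common to both arms. That part cancels in the contrast, so its variance is 225 × [(1 − ICC)/100 + (1 − s) × ICC/K + (1 − s × ICC)/100].
- s = 0.5, K = 10: type I error 5.4 % (ICC 0.02) and 6.0 % (ICC 0.05).
- s = 0.5, K = 5: 6.0 % and 7.5 %.
- s = 1: 4.8 % and 4.4 % for either K, so no inflation.

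**Step 4, power by type of test.** The planned unadjusted ANCOVA has power Φ((6 − 1.96 × 2.12) / true SE). For 5 clubs of 20 this is about 79 % at ICC 0.02 and 76 % at ICC 0.05. A test adjusted for a known ICC has 74 % and 64 %. With Satterthwaite degrees of freedom (about 12 and 9) power falls to about 66 % and 55 %, and it is about 75 % even at ICC 0. For 10 clubs of 10 the Satterthwaite figures are about 78 %, 75 % and 69 % at ICC 0, 0.02 and 0.05.

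**The case against.** The strongest reply is that the protocol never shows clustering. It gives no ICC, number of clubs or club size, and says only that football may bring peer support. Small-sided play is 20 of 60 minutes, fixed teams are not described, and men who never attend are exposed to neither coach nor team-mates, which dilutes any correlation. At ICC 0.01 the effect is small. All of this stands. A reader might infer that outcomes are in fact correlated within clubs; the documents support only the conditional statement.

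Second, randomisation is stratified by centre. Differences common to both arms of a centre cancel, and leaving centre out makes the standard error too large for that part. This also stands, and Step 3 shows how far it lowers the figures.

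Third, the inflation presumes club effects that average zero but differ between clubs. If the offer of football changes nobody's outcome, no club correlation is induced by it and the planned test holds its level. Treating clubs as a sample from a wider population is also a choice. The protocol targets a policy of offering football and speaks of generalisability, without stating that inference is to clubs at large. I regard that as the natural reading of its aims, but the protocol should say so.

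Fourth, a reader might take 64 % as the power of the planned analysis. It is not: that figure belongs to an adjusted test, and the planned one has about 76 % in the same setting.

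**Conclusion.** The point holds as a conditional one. Delivery is grouped in one arm, the specified models have no club or centre term, and the sample size assumes independence. If club outcomes differ in the football arm, the reported standard error is too small and the 5 % level is not kept.

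For the club sizes hinted at (10 to 14 men), ICC 0.01 to 0.05 and all clustering in the football arm, the true standard error is 2 to 15 % larger and type I error is 5.5 to 8.9 %. The 10.7 % figure needs 5 clubs of 20 and ICC 0.05, so it is the upper end of the range considered and not the expected value. With half of the clustering shared by centre, the 10- and 5-club settings at ICC 0.02 to 0.05 give 5.4 to 7.5 %; with all of it shared there is no inflation.

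The stated 100 per group is not an arithmetic error, since it reproduces. It has no allowance for clustering, and the sample size section states none for dropout that could absorb the loss.

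**What to change.** - Add centre, already a stratification factor, to the primary and secondary models.
- Fit a random club intercept in the football arm only (zero for controls) with Kenward-Roger or Satterthwaite degrees of freedom, as the primary model or at least as a pre-specified sensitivity analysis. Report the club ICC.
- Assign each man in the football arm the club offered to him at allocation, so that men who never attend keep a club under intention-to-treat. The protocol describes attendance recording by coaches, not club assignment, so the club offered should be recorded explicitly.
- State that 80 % power holds only under independence. A test adjusted for a known ICC has about 77 to 79 % (10 men per club) or 74 to 77 % (20 men per club) at ICC 0.01 to 0.02, and 72 % or 64 % at ICC 0.05. It is lower with small-sample degrees of freedom and few clubs.

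**Cost:** analysis wording, plus a power statement. The downside is a wider interval and fewer degrees of freedom even if the true club variance is zero (about 75 % power with 5 clubs). Protection is also partial: with few clubs the variance may be estimated as zero when it is not, and the model then falls back to the planned ANCOVA plus centre.

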### Control group

Participants allocated to the control group will receive a phone-based counselling session (5–15 min) as part of the information on group allocation, as well as information via email on the current physical activity guidelines.

### Outcomes

The *primary outcome* is change in PCa-specific QoL from baseline to 12 weeks measured with the fourth version of the Functional Assessment of Cancer Therapy–Prostate (FACT-P) questionnaire [28], a self-reported, multidimensional QoL instrument specific for PCa patients [29]. The questionnaire consists of 27 general cancer items covering four domains - physical, social/family, emotional and functional well-being - supplemented with 12 specific PCa-related items. All items are scored on a 0–4 Likert scale. The total FACT-P score ranges from 0 to 156, higher scores indicating higher QoL.

Table 3 presents all outcomes with specified measurement variable, analysis metric, method of aggregation and time point.

The 12-Item Short Form Health Survey (SF-12) and EQ-5D-5 L, a standardised instrument by EuroQol for use as a measure of health outcome, will be collected for use in later economic evaluations of the intervention.

[figure not shown]**Fig. 1** Trial design and timeline

**Table 2** Logic model: The FCPC Trial

| Inputs (resources)                                                                                                                                                                                                                                                                                                                                                                                                                                                      | Activities                                                                                                                                                                                                                                                                                                                                                         | Outputs                                                                                                                                                    | Outcomes (short-term)                                                                                                                                                                                                                                                 | Impacts (long term)                                                                                                                                                                                           |
|-------------------------------------------------------------------------------------------------------------------------------------------------------------------------------------------------------------------------------------------------------------------------------------------------------------------------------------------------------------------------------------------------------------------------------------------------------------------------|--------------------------------------------------------------------------------------------------------------------------------------------------------------------------------------------------------------------------------------------------------------------------------------------------------------------------------------------------------------------|------------------------------------------------------------------------------------------------------------------------------------------------------------|-----------------------------------------------------------------------------------------------------------------------------------------------------------------------------------------------------------------------------------------------------------------------|---------------------------------------------------------------------------------------------------------------------------------------------------------------------------------------------------------------|
| Financial resources 
 
• Funding
 
 Human resources 
 
• Urologist and urological nurses
 
• Local experienced football coaches
 
 Products 
 
• Football-training manual
 
• Disease specific football-coach education
 
• Tablet based app to register attendance and field-test performance
 
 Planned work | 
 
• Collaboration with local football clubs
 
• Education of local coaches
 
• Collaboration with urological clinics
 
• Information to clinical staff and patients' on the possibilities of referral for the study
 
• Provision of feedback on attendance and progress (field tests)
 
 | 
 
• Prostate cancer patients referred to and participating regularly in football training
 
 Intended Results | Improved: 
 
• Quality of life
 
• Physical activity level
 
• Fat mass
 
• Muscle mass
 
• Bone mineral density and content
 
• Functional well-being
 
• Dyadic adjustment
 
 | Improved: 
 
• Survival
 
 Reduced: 
 
• Co-morbidities
 
• Hospital admissions
 
• Medication usage
 
 |

